**Figure 4 F4:**
[figure not shown]
shows 150 blocks with a partitioned box that will be used for BBT

**Secondary outcome measures:** ABILHAND-Kids will be used to evaluate upper extremity function. It is a 21-item functional ordinal scale specifically developed to measure manual ability in children with CP. Its measurement precision is considered highly adequate for clinical practice. Parents are requested to fill the questionnaire on the basis of their perception of the level of difficulty that a child faces during the performance of each activity in the list on a three-tier scale of `impossible´, `difficult´, `easy´ [11]. The linear measures obtained by the Rasch model can be used to make a comparison quantitatively regarding the manual ability of children with CP [12]. The test has shown excellent test-retest reliability as well as internal consistency [11]. It has excellent convergent validity with MACS [13]. WeeFIM (self-care section) will be used for evaluating functional independence. Functional independence measure for children is also known as WeeFIM. It can be used to estimate the `burden of care´ for children with developmental disabilities between 6 months to 21 years of age [14]. The performance of task is categorized as `dependent´ if the score is between 1-5 and is categorized as `independent´ if the score is 6 or 7. Score 1 indicates total assistance, score 2 indicates maximal assistance, score 3 indicates moderate assistance, 4 indicates minimal assistance, score 5 indicates supervision or set-up, score 6 indicates modified independence that includes an assistive device usage or not completing the task in a timely or safe manner and score 7 indicates complete independence i.e. the child completes the task without using a device [14]. The test-retest reliability is excellent for children with disabilities [15].

**Sample size:** sample size of 36 was calculated with 90% of confidence interval considering the dropouts, with 18 participants in each group by using G*Power software. A convenient sampling technique will be used.

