**Recruitment and allocation:** potential participants will be screened for eligibility criteria and after obtaining well-informed written consent of the parent(s) or legal guardian, the child will be recruited as a participant. The participants will be distributed in 1: 1 manner into experimental group/group A (VR and haptic feedback in addition to the conventional physiotherapy) and control group/group B (conventional physiotherapy only).

**Data collection:** pre-intervention data will be collected using predetermined primary and secondary outcome measures. The training would be carried out for 6 weeks (5 days a week). The duration of each session would be 60 minutes. Virtual reality and the haptic feedback with conventional physiotherapy, and conventional physiotherapy alone are independent variables. Upper extremity function and functional independence are dependent variables. Data collected will be noted down and will be placed in a tabular format.

**Statistical methods:** after consultation with the statistician, statistical analysis will be done by using descriptive and inferential statistics using t-test, Wilcoxon signed-rank test and Mann-Whitney U test. Software SPSS 27.0 version and GraphPad prism 7.0 version will be used in the analysis. The changes in the outcome measures brought about after the course of 6 weeks of intervention will be analyzed by mixed-effects linear models across `time´ (pre-intervention vs post-intervention) and `group´ (experimental vs control). The age of participants and baseline scores of outcome measures between the two groups will be compared using t-tests. A p-value of less than 0.05 will be considered as level of significance. If subjects are lost to follow-up, an intention-to-treat analysis will be carried out. The results will be interpreted to note any significant statistical and/or clinical differences. The results will be accounted and documented as per the CONSORT guidelines.

**Trial design:** this is an interventional, non-randomized, active controlled, superiority trial with allocation ratio of 1: 1 in experimental group and control group.

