On the other hand, the VR-based rehabilitation is designed to offer therapy is characterized by repetitive task-specific movements that include abduction and opposition of the thumb, which is often difficult for children with hemiplegic CP on the affected side. Haptic feedback finely tunes the motor response within a virtual environment, and the children are expected to look forward for such enjoyable sessions to tap their high neuroblastic potential. Play station is a motivational training tool for children with CP and has the potential to improve UE function [20]. The primary outcome measures will assess the manual dexterity (9HPT and BBT) and secondary outcome measures (ABILHAND-Kids and WeeFIM) will assess the functional independence that are hypothesized to be gained by haptic enhanced VR intervention when combined with the conventional therapy. The advantages of the haptic enhanced VR study include the customized approach towards the rehabilitation protocol and the responsiveness of the VR system during the intervention. To avoid any disparity between the two groups, the total rehabilitation time will be the same for both groups. The results of the study will aid the children with unilateral CP in the future by providing a fun way of utilizing the advanced technology of rehabilitation.

**Limitations:** this study will not focus on participation of the child in the society in context of International Classification of Functioning, Disability, and Health (ICF). Long term follow up to observe maintenance or regression of the possible effects will not be carried out. Investigator is not blinded.

**Probable implications:** motor learning principles are well knit in context of VR along with force/tactile feedback that would help the children in learning skills related to manual dexterity. If the children show improvement in their hand function, burden of care on the caregivers will decrease as the child will become independent in activities of daily living. The study may pave the way for further advancement of technology for the use in younger children with infantile hemiplegia for early intervention.

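### Allocation is declared non-random with no stated rule or reason, so the planned superiority and efficacy conclusion is open to selection on expected improvement, which the planned analysis does not address

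*Protocol article*

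**What the plan says.** All places are in the protocol article.

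- **Trial design (Methods):** "this is an interventional, non-randomized, active controlled, superiority trial with allocation ratio of 1: 1".
- **Recruitment and allocation:** consent comes first: "after obtaining well-informed written consent of the parent(s) or legal guardian, the child will be recruited as a participant". Then "The participants will be distributed in 1: 1 manner into experimental group/group A" and group B. The section names no rule and nobody who assigns.
- **Table 1:** GMFCS, MACS and all four outcome measures are in the enrolment column, before allocation. Severity and starting scores can therefore be known before a child's group is fixed.
- **Sample size (Methods):** the article reports that "sample size of 36 was calculated with 90% of confidence interval considering the dropouts, with 18 participants in each group by using G*Power software".
- **Statistical methods:** pre-to-post changes are analysed by mixed-effects linear models over time and group. Age and baseline outcome scores are compared by t-tests. The significance level is 0.05. MACS and GMFCS are not mentioned.
- **Discussion:** the stated aim is to estimate efficacy against conventional physiotherapy alone. Equal total therapy time is the one step offered for keeping the groups comparable. The limitations cover participation outcomes, long-term follow-up and blinding ("Investigator is not blinded"). Non-random allocation is not among them.

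**The concern.** The trial is prospective, at one centre, with 36 children who are consented and tested before they are assigned. Nothing in the article stands in the way of randomising, and no reason for not doing so is given. The central comparison therefore rests on groups formed by an undescribed non-random process.

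The article's own rationale makes selection plausible. It presents virtual reality as motivating, and a child's eagerness is also a natural reason to place that child in the gaming group. Motivation is not among the baseline variables in Table 1, so it cannot be adjusted for. Both primary outcomes, the nine-hole peg test and the box and block test, are performance tests. A group that would have improved more under any therapy could show a difference that is then read as an effect of the intervention.

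**Working it through.** **No stated figure to reproduce.** The point rests on the declared design. The arithmetic below shows how much protection the planned safeguards give.

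**Inputs.** From the article: 18 per group and level 0.05. Assumed: two-sided testing (sidedness is not stated), complete data, and the imbalances d.

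**Step 1: what the planned model removes.** With two complete time points, the time-by-group contrast of a mixed model is the comparison of mean change between groups. A stable gap in starting level is present before and after, so it cancels. As a check, 20,000 trials of 36 children were simulated with no treatment effect. Stable ability drove both tests equally (pre-post correlation 0.8, assumed), and a child of above-median ability entered group A with probability 0.60 or 0.65.

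| Probability | Rejects on post score alone | Rejects on change |
|---|---|---|
| 0.60 | about 14% | about 5% |
| 0.65 | about 25% | about 5% |

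The planned model therefore handles this form of selection.

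**Step 2: what it does not remove.** Selection on the amount a child will improve appears directly in the change. For a two-sample t-test with 18 per group:

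- degrees of freedom = 2 × 18 − 2 = 34, critical value 2.032
- noncentrality = d × √(18/2) = 3d
- rejection rate = P(|T| > 2.032), with T noncentral t

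| d (SD) | 3d | Rejection rate |
|---|---|---|
| 0 | 0 | 5% |
| 0.2 | 0.6 | 9% |
| 0.3 | 0.9 | 14% |
| 0.5 | 1.5 | 31% |
| 0.8 | 2.4 | 65% |

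Read with d as the residual difference in the analysed change and no true effect, these are false-positive rates. More children would not help, because the noncentrality d√(n/2) grows with n.

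**Step 3: the baseline t-tests.** The same table, with d as a true baseline imbalance, gives their power: 14% at 0.3 SD, 31% at 0.5 SD and 65% at 0.8 SD. A non-significant baseline test does not show that the groups are comparable.

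**Step 4: how steering becomes a residual difference.** For a normal latent score, the means of the upper and lower halves are ±0.798 SD. If children above the median enter group A with probability p and those below with 1 − p, the gap between groups is 2 × 0.798 × (2p − 1). This is 0.32 SD at p = 0.60 and 0.48 SD at p = 0.65. Only the part that carries into the change counts. If the latent score correlates 0.5 with the change, gaps of 0.3 and 0.5 SD become 0.15 and 0.25 SD, and the rejection rates are about 7% and 11%.

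**The case against.** The strongest reply is that non-randomisation is openly declared, had ethics approval, and is accompanied by a pre-post model and a baseline comparison. Part of this stands. The pre-post model deals with stable differences in starting level, so it would be wrong to say that treatment and selection cannot be separated at all. It does not deal with differences in expected improvement, and declaring the design does not remove the bias.

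Several stronger readings are tempting, and the article does not support them:

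- **Allocation is unconcealed.** The article is silent. A condensed article may leave the procedure to a full protocol that is not shown.
- **The unblinded investigator assigns the children.** The limitations say only that the investigator is not blinded. Nobody is named as assigning.
- **Families choose the group.** Nothing says so.
- **Convenience sampling is itself the flaw.** "A convenient sampling technique will be used" concerns who is recruited, and so bears on generalisability more than on how recruited children are divided.
- **CONSORT reporting contradicts the design.** The article plans that "The results will be accounted and documented as per the CONSORT guidelines", but the non-random design is declared openly right after it. Superiority names the type of hypothesis, not the method of allocation.
- **False-positive rates of 14% and 31% are to be expected.** They apply only if the whole of a 0.3 or 0.5 SD gap reaches the analysed change. With partial transfer they are lower, and with selection on stable level alone the rate is near 5%.

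**Conclusion.** The concern holds as a weakness in a stated design choice. Allocation is declared non-random with no rule or reason in the article, while the trial aims at superiority and efficacy and omits this limitation. The planned analysis covers stable starting differences but not selection on improvement. It names neither MACS nor GMFCS, and its baseline tests are too weak at 18 per group to give reassurance.

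The size depends on an unknown. If the residual difference in change is between 0 and 0.5 SD, the two-sided false-positive rate runs from 5% to about 31%. The article gives no basis for choosing a point in that range. The calculation assumes two-sided testing, complete data and a comparison of change. The point matters because selection on unmeasured factors cannot be repaired once children are assigned.

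**What to change.** **Preferred.** Change the Trial design and the Recruitment and allocation sections to randomised 1:1. Use a computer-generated, concealed list prepared by someone who does not recruit, for example the statistician already consulted. Reveal each assignment only after consent and baseline testing, an order that Table 1 already follows. Stratifying by MACS is optional.

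**If randomisation is not possible.**
- State the allocation rule.
- Adjust the model for age, MACS, GMFCS and baseline score. These need to enter as covariates for the change (or as covariate-by-time terms), because with two complete visits a main effect alone leaves the time-by-group estimate unchanged.
- List non-random allocation as a limitation.
- Word the conclusion as an adjusted association and not as proof of superiority.

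The fallback reduces bias from measured factors only.

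**Cost.** Randomising needs a protocol, ethics and registry amendment and one allocation list, with no extra children, visits or staff. The fallback needs changes to the text and the analysis.

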## Discussion

Virtual reality (VR) has emerged as a promising intervention for improving motor function in children with CP in a few previous studies, though groups were heterogeneous with a small sample size [6,16,17]. The proposed study aims to estimate the efficacy of haptic enhanced VR with conventional physiotherapy compared to only conventional physiotherapy in improving upper extremity (UE) function and functional independence in school-aged children with hemiplegic CP. Diminished motor control of the affected upper extremity leads to neglect and learned disuse by the child that hampers its sensory-motor development [18]. The vicious cycle of weakness and disuse needs to be broken for improving function, which is usually a challenging task for children with infantile hemiplegia who are otherwise ambulatory. Gross and fine motor dexterity, as well as the use of paretic hand in bimanual activities, is the major area of concern of most parents. Though constraint induced movement therapy has been considered effective in the management of infantile hemiplegia, it lacks the much-needed motivation for the child that limits the number of repetitions of movements and the long-term compliance [19].

On the other hand, the VR-based rehabilitation is designed to offer therapy is characterized by repetitive task-specific movements that include abduction and opposition of the thumb, which is often difficult for children with hemiplegic CP on the affected side. Haptic feedback finely tunes the motor response within a virtual environment, and the children are expected to look forward for such enjoyable sessions to tap their high neuroblastic potential. Play station is a motivational training tool for children with CP and has the potential to improve UE function [20]. The primary outcome measures will assess the manual dexterity (9HPT and BBT) and secondary outcome measures (ABILHAND-Kids and WeeFIM) will assess the functional independence that are hypothesized to be gained by haptic enhanced VR intervention when combined with the conventional therapy. The advantages of the haptic enhanced VR study include the customized approach towards the rehabilitation protocol and the responsiveness of the VR system during the intervention. To avoid any disparity between the two groups, the total rehabilitation time will be the same for both groups. The results of the study will aid the children with unilateral CP in the future by providing a fun way of utilizing the advanced technology of rehabilitation.

**Limitations:** this study will not focus on participation of the child in the society in context of International Classification of Functioning, Disability, and Health (ICF). Long term follow up to observe maintenance or regression of the possible effects will not be carried out. Investigator is not blinded.

**Probable implications:** motor learning principles are well knit in context of VR along with force/tactile feedback that would help the children in learning skills related to manual dexterity. If the children show improvement in their hand function, burden of care on the caregivers will decrease as the child will become independent in activities of daily living. The study may pave the way for further advancement of technology for the use in younger children with infantile hemiplegia for early intervention.

## Conclusion

The interpretation of the results of the study will help to gain a better understanding of the utility of haptic enhanced VR based physiotherapy intervention in children with hemiplegic or unilateral CP.
